#### Static MRI

Static MRI will just take the neutral position of cervical spine. Static MRI is the routine examination for CSM patients and could demonstrate the disc, vertebrae, cerebral spinal fluid (CSF), spinal cord and the abnormal signal in spinal cord. In this study, the degree of spinal cord compression on static MRI will be assessed according to the three-level classification described above. Also, T2-HIS will be a parameter and collected as exist or non-exist.

#### Dynamic MRI

Dynamic MRI will show the flexional and extensional position of cervical spine other than neutral position. The angle of extension and flexion is as can be tolerated and it will take longer time than static MRI. The extension and flexion are accomplished by a self-designed posture cushion (Fig. 2). All participants in this study will receive dynamic MRI after informed consent for free. The same evaluation as static MRI will be carried out for dMRI.

**Fig. 2 Fig2:**
[figure not shown]
The extension and flexion of cervical spine

#### Surgical intervention

According to the article review by Zhu et al. [20] from our institution, the surgical intervention for CSM was still controversial. Generally, the surgical approaches for CSM can be divided into anterior and posterior approaches. Anterior procedures include discectomy and corpectomy. Posterior procedures include laminoplasty and laminectomy (Table 1). In some cases, combined approach will be necessary.

**Table 1 Tab1:** surgical options

Surgical approach	Procedures
Anterior	Discectomy and corpectomy
Posterior	Laminoplasty and Laminectomy
Combined	

The level to decompression would be largely determined by patient history, physical examination findings, X-rays, CT, and conventional MRI, and dMRI would always be interpreted with the grain of salt that the compression levels might be increased by dMRI, particularly with neck extension. Additionally, the general condition and expectation of patients will also be taken into consideration before making surgical decision.

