**Method:**

A total of 180 CSM patients who have indications for surgery will be recruited in outpatient of Peking University Third Hospital and assigned to three groups (Group A, B and C) based on their static MRI after consent. Group A (incomplete dura compression) means the signal of cerebral spinal fluid (CSF) is still visible. Group B (complete dura compression) means no CSF signal and no shape change of spinal cord. Group C (spinal cord compression) means shape change of spinal cord. Two surgical plans will be made for each participant by one professional surgeon according to the static MRI and dynamic MRI respectively and we will randomly choose one to perform via a random number system. Follow-up will be maintained at 3, 6, and 12 months after surgery through outpatient or telephone interview, including mJOA score, 10-s G&R (grip and release) and 10-s step test, SF-36 score, radiographic examination and complications. Finally, data collection and statistical analysis will be finished by researchers who are blinded to recruitment and treatment.

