### Randomization

Patients will be recruited from outpatient and eligible participants will be enrolled in the study after informed consent. The treating surgeon will also confirm the eligibility before making two surgical plans based on the static MRI and dMRI, respectively. A researcher will randomly choose one from the two surgical plans via a random number system. Randomization of experiment group (dMRI) and control group (static MRI) will be on a 1:1 basis.

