### Blinding

As the surgical plans should be informed to patients clearly, the patients cannot be blind to their surgery. However, all patients won’t know which MRI the surgical plan is from. In addition, the treating surgeon will also not be blind to the treatment but will not take part in the preoperative and postoperative research assessment. The clinical outcome data will be collected by independent research assistants who are blind to the surgical decision making.

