### Interventions

The surgical indication of Patients with CSM is mainly based on the symptoms, physical and radiographic examination. All participants will receive routine examination at admission, including blood routine and evaluation of general condition. Imaging examination as X-ray, CT and MRI will be accomplished before making surgical plan. All patients will receive imaging examination immediately after surgery and follow-up will be continued at 3, 6 and 12 months after surgery. This trial will involve two types of MRI: static MRI and dynamic MRI. These two types of MRI will be performed in the supine position.

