### Data management

All participants will receive a study number and all data about patients will be recorded via this number. All information about participants including baseline information, radiographic outcomes, surgery and follow-up will be secured in Peking University Third Hospital. Data will be collected at baseline admission and 3, 6 and 12 months after surgery. One professional surgeon will make the surgical plan and finish the surgery in Peking University Third Hospital. The researchers will collect the baseline information and maintain the follow-up after surgery. Data entry, transfer and subsequent maintenance will be performed by a data manager. Access to study data is restricted to the study research team.

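### One surgeon not blind to treatment writes both randomised plans after imaging is complete, and nothing in the level-selection text keeps dynamic MRI findings out of the static-MRI plan

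*Protocol article*

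**What the plan says.** The Abstract (Method) sets out the contrast: "Two surgical plans will be made for each participant by one professional surgeon according to the static MRI and dynamic MRI respectively", with one plan then chosen at random. Validation research repeats this, and Randomization speaks of "making two surgical plans based on the static MRI and dMRI, respectively". Each plan therefore has a named source.

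The other relevant statements in the Protocol article are:

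- Data management: "One professional surgeon will make the surgical plan and finish the surgery".
- Interventions: "Imaging examination as X-ray, CT and MRI will be accomplished before making surgical plan", and "This trial will involve two types of MRI: static MRI and dynamic MRI". Dynamic MRI adds that every participant has the dynamic scan.
- Blinding: "the treating surgeon will also not be blind to the treatment".
- Surgical intervention, on choosing levels: "The level to decompression would be largely determined by patient history, physical examination findings, X-rays, CT, and conventional MRI", followed by the caution that "dMRI would always be interpreted with the grain of salt that the compression levels might be increased by dMRI, particularly with neck extension".

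Statistical analysis specifies ITT. No section says in what order the two plans are written, when the flexion/extension images reach the surgeon, or whether the static plan is fixed before they do. The listed outcomes compare the images (compression degree, number of compressed levels, T2 high-intensity signal) and follow the patient, but none records whether the two plans differ.

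**The concern.** The mJOA comparison tests whether planning from dMRI leads to better recovery than planning from static MRI. That requires the control plan to be the one the surgeon would have written without the dynamic images. If the same surgeon has already seen cord compression in extension, the static plan may be pulled towards the dMRI plan. The control arm then receives part of the intervention.

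A patient whose two plans match in levels, approach and procedure has the same operation whichever is drawn, and contributes nothing to the expected difference between arms. If the result is null, the reader cannot tell whether dMRI-based surgery fails to help or whether the plans seldom differed. This bears on the validation part's stated interest in surgical decision making. The within-patient image comparison of the feasibility part is not affected.

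**Working it through.** **The text side by side.** The Abstract, Validation research and Randomization name a source for each plan. Surgical intervention gives one account of level selection without saying which plan it governs. Interventions places imaging before planning, Data management has one surgeon do the planning, and Blinding leaves that surgeon unblinded to treatment. Together they permit dMRI findings to reach the static plan. They do not say that this happens.

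**The plan's own figure.** Sample size calculation gives 180 patients, means of 60.8% and 85% (difference 24.2 points), a two-sided t-test, type I error 0.025, type II error 0.1, 1:1 allocation and 20% dropout. No standard deviation (SD) is given, so 180 cannot be reproduced. Solving back:

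- Evaluable patients: 180 × 0.8 = 144, or 72 per arm.
- z(0.9875) + z(0.90) = 2.2414 + 1.2816 = 3.523.
- Implied SD = 24.2 / (√(2/72) × 3.523) = 41.2 points.

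The steps below need only the ratio of planned effect to standard error, 3.523, and not the SD itself.

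**Illustrative dilution.** Let c be the share of wholly identical plan pairs. The documents do not give c, so 10%, 25% and 50% are assumed values. Assume also that the planned effect holds where plans differ, that there is no effect elsewhere, and that the SD is the same throughout.

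- ITT difference = (1 − c) × effect where plans differ.
- ITT power = Φ((1 − c) × 3.523 − 2.2414).
- Sample-size multiplier = 1/(1 − c)².
- Power among patients whose plans differ = Φ(√(1 − c) × 3.523 − 2.2414).
- Standard error of that comparison, relative to the full sample = 1/√(1 − c).

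| c | ITT power | Sample multiplier | Patients with differing plans, of 144 | Power among them | SE multiplier |
|---|---|---|---|---|---|
| 10% | 0.824 | 1.23 | 130 | 0.864 | 1.05 |
| 25% | 0.656 | 1.78 | 108 | 0.791 | 1.15 |
| 50% | 0.316 | 4.0 | 72 | 0.599 | 1.41 |

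If 90% power is instead planned at two-sided 0.05, the significance level in Statistical analysis, ITT power is 0.831, 0.681 and 0.367.

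**What the lock could recover.** Split c into c0 (agreement because dMRI adds nothing or is read with caution) and c1 (agreement because dMRI findings entered the static plan). Without a lock the ITT difference is (1 − c0 − c1) times the effect where plans differ. With a lock it is (1 − c0) times that effect. Only c1 is contamination, and the documents give neither part. Leakage that shifts the static plan without making the two plans identical is not captured by c at all.

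**The case against.** The strongest reply is that three places already tie each plan to its own scan, so the caution about dMRI reads naturally as guidance for the dMRI plan alone. The statement on imaging concerns when scans are done, not what the surgeon looks at. Being unblinded to treatment is not the same as having every image open while writing the control plan. Reading order and form entries may also sit in the full protocol.

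Much of this stands. A reader might infer that the surgeon will use dMRI in the static plan. The article does not say so; access is an inference from the sequence described. A reader might also take the cautious reading of dMRI as an error. It is not: a strategy of cautiously read dMRI is legitimate, and ITT estimates its overall effect. Plans that agree on levels can still differ in approach or implants, and the Discussion cites a study in which 3 of 4 reviewers selected significantly more levels after seeing dMRI, so divergence is plausible.

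The reply does not close the gap. Naming a source for each plan does not stop one person who may have seen everything from drawing on it. The only level-selection text blurs the separation that the other sections imply. Blinded assessors protect the measurement of outcome, not the content of the control plan. The recorded imaging findings show how far the scans differ, not whether the plans do.

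**Conclusion.** The point holds as a weakness in how the control plan is protected. As written, dMRI findings can enter the static-MRI plan, which would narrow the randomised mJOA contrast by an unknown amount, and a null ITT result would be hard to interpret without a record of plan agreement.

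A reader might infer from the table that the trial is underpowered by a known margin. The documents do not support that. The share of identical plans is not given. Agreement because dMRI adds nothing, or is read with caution, belongs to the strategy effect and is no loss. The 60.8% and 85% are stated for whole groups, so the planned effect may already average over patients with identical plans, in which case that agreement costs no power against the plan. The figures of 82%, 66% and 32% therefore illustrate how sensitive the ITT comparison is to identical plans under one reading. They are neither an estimate of the harm nor what the fix would recover. The correction is worth making because it is cheap and closes a real route of contamination.

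**What to change.** In Surgical intervention, state that both plans use the same history, examination, X-ray, CT and neutral MRI; that the static-MRI plan is completed and locked before the surgeon views the flexion/extension images; and that only the dMRI plan adds those images, with clinical caution allowed.

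Before the random draw, record whether the two plans differ in levels, approach or procedure. Keep ITT in all patients as the primary analysis and report the share of identical plans. Add a prespecified supportive comparison of the randomised arms among patients whose plans differ. It remains a randomised comparison because both plans are fixed before the draw.

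The cost is a small change in workflow to hold the dynamic images back, one form entry per patient and a few sentences of text. No extra patients, scans or procedures are needed. The supportive estimate is less precise than one from the full sample, as the last column of the table shows.

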### Outcome measures

All participants will be assessed by research assistants who are blinded to the allocation and analysis at different time points shown in Table 2. In addition, the general information including age, gender, weight, symptoms, duration and previous treatment and medication will be confirmed at the admission.

**Table 2 Tab2:** Time schedule

Measure	Admission	3 months	6 months	12 months
mJOA score	╳	╳	╳	╳
SF-36	╳	╳	╳	╳
G&R and step test	╳	╳	╳	╳
X-ray examination	╳	╳	╳	╳
Static MRI	╳			
Dynamic MRI	╳			

### Primary outcome

#### Cord compression degree

We have discussed the difference of cervical canal stenosis between static MRI and dMRI in the previous study [13]. Dynamic MRI with cervical extension could reveal higher stage of spinal cord compression [9, 11, 15, 21]. All participants in this study will receive static MRI examination after admission and there are three levels of cord compression based on the sagittal and transverse images, including incomplete dura compression, complete dura compression and spinal cord compression. After consent, all participants will receive dynamic MRI examination demonstrating the flexion and extension of cervical spine. The same classification of cord compression will also be applied to dynamic MRI. Meanwhile, the number of levels under moderate to severe compression is also important and we will record this together with cord compression degree.

#### mJOA

The modified Japanese Orthopaedic Association score (mJOA) is a commonly used research tool in the evaluation of cervical myelopathy. It is comprised of 4 domains that evaluate motor function of the upper and lower extremity, sensory function of the upper extremity and bladder function. Previous studies have demonstrated that the mJOA has the validity of evaluation for CSM patients after surgery [22, 23].

The treating clinical team will evaluate the mJOA score for all CSM patients before surgery. The treating clinicians will not be part of the research team. At 3, 6 and 12 months after surgery, mJOA will be assessed via either outpatient or telephone interview during follow-up. The improvement rate of mJOA score at 3, 6, and 12 months compared to baseline will be calculated finally.

### Secondary outcome

#### T2-his

For CSM patients, T2-HIS (T2 high-intensity signal) and decreased signal intensity on T1-weighted MRI are well-known changes in spinal cord lesions. A study showed that the preoperative and postoperative evaluation of CSM patients were better in the patients without T2-HIS compared with patients with T2-HIS. However, T2-HIS grading was not associated with the severity of myelopathy and outcomes, which was reported in the static MRI research [24]. In this study, we will also collect the T2-HIS on the compression segment of static MRI and the extension-flexion position on dMRI, including the length and levels of T2-HIS.

#### SF-36

The SF-36 is a multipurpose, short-form health survey with only 36 questions. It yields an eight-scale profile of scores as well as physical and mental health summary measures [25]. Accordingly, the SF-36 is commonly recommended for the evaluation of quality of life in CSM patients [26]. The treating clinicians will evaluate the SF-36 for all participants after admission. At 3, 6 and 12 months after surgery, SF-36 will also be assessed during follow-up.

#### 10-s G&R and 10-s step test

The mJOA score alone may be insufficient to effectively assess the neurological condition in CSM. The 10-s grip and release (G&R) test and 10-s step test were reported to be useful tools to evaluate the severity of cervical myelopathy quantitatively. These tests were useful for quantitatively evaluating the surgical outcomes in CSM [27, 28].. For the 10-s G&R test, each patient will be asked to G&R with the fingers as rapidly as possible with the forearm kept in pronation and the wrist in mild extension. For the 10-s step test, each patient will be asked to take high steps by bending their knee 90°,making their thighs parallel to the floor. They will be asked to take as many of these steps as they could in place, without holding on to anything for balance for 10-s [24, 29].

#### Radiographic outcomes

The cobb angle between C2 and C7 will be measured before surgery and at 3, 6 and 12 months after surgery during follow-up in the neutral and maximal flexion-extension lateral radiographic view. The fusion and cage subsidence will be recorded as descriptive outcome in the Case Report Form. Cage subsidence in anterior approach is defined as decrease in the total intervertebral height (TIH) between two fused vertebral bodies comparing to the first postoperative radiographs. Usually, decrease in TIH ≥ 3 mm is defined as significant subsidence [30].

#### Complications

All complications and interventions related to the evaluation and treatment for participants will be recorded.

### Adverse event management

Adverse events (AEs) are defined as any untoward medical occurrence in a clinical trial subject and which do not necessarily have a causal relationship with the treatment. In this study, the extra interventions for participants who are willing to receive surgery are dynamic MRI and function assessment, which are non-invasive and safe. The events related to surgery and other diseases which have no correlation with CSM will be counted as the complications and system disease. All participants Experiencing Significant Adverse Events (SAEs) will be followed up as per protocol until the end of the trial.

### Data management

All participants will receive a study number and all data about patients will be recorded via this number. All information about participants including baseline information, radiographic outcomes, surgery and follow-up will be secured in Peking University Third Hospital. Data will be collected at baseline admission and 3, 6 and 12 months after surgery. One professional surgeon will make the surgical plan and finish the surgery in Peking University Third Hospital. The researchers will collect the baseline information and maintain the follow-up after surgery. Data entry, transfer and subsequent maintenance will be performed by a data manager. Access to study data is restricted to the study research team.

### Safety

Participants in this study are going to receive surgical treatment. All extra interventions except surgery in this study are non-invasive but there is the possibility of neurological deterioration with the several minutes for neck extension position, which will be explained to patients when obtaining the consent. The angle of extension and flexion during dMRI is just as the patients can tolerate and there will be a researcher to assist during the examination. Moreover, all expected or unexpected adverse events from this study will be recorded and monitored. Patients suffered from this study will also receive free treatment.

### Sample size calculation

The sample size is calculated with reference to previous study and based on the sample size calculation formula. The average mJOA score improvement rate of surgical treatment according to static MRI in our hospital was 60.8%. we assume that the mJOA score improvement rate12 months after surgery in group dynamic MRI is 85%. We will recruit a sample of 180 participants including three groups stratified according to the spinal cord compression of static MRI. One hundred and eighty is based on a two-sided t-test, a type I error at 0.025 and type II error at 0.1 after taking into consideration a 1:1 allocation rate and a dropout rate of 20%.

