### Statistical analysis

Pre-treatment baseline characteristics will be compared between randomized groups to monitor the chance imbalances. Statistical analyses will be performed following the intention-to-treatment (ITT) analysis. The experimental arm (dMRI) will be compared against the control (static MRI) for all primary analysis. We will use chi-squared test for binary outcomes and T-test for continuous outcomes. Spearman’s correlation coefficient will be used to analyze the correlation between the mJOA improvement rate and covariates. A value of *P* < 0.05 will be reported as statistically significant. All analysis will be carried out using SPSS 20.0 software by a researcher blinded to the recruitment and collection.

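### The sample size uses a two-sided type I error of 0.025 but the analysis declares significance at P < 0.05, and mJOA is listed as primary at three visits although only 12 months was sized

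*Protocol article*

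**What the plan says.** All places are in the protocol article.

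- **Sample size calculation.** The error rates are given as: "One hundred and eighty is based on a two-sided t-test, a type I error at 0.025 and type II error at 0.1". Allocation is 1:1 and dropout 20%. The control mJOA improvement rate is 60.8%. For the experimental arm the section says: "we assume that the mJOA score improvement rate12 months after surgery in group dynamic MRI is 85" (per cent). No standard deviation is given; the only source is: "The sample size is calculated with reference to previous study and based on the sample size calculation formula".
- **Statistical analysis.** The threshold is P "< 0.05 will be reported as statistically significant". No exception is made for the primary comparison. The section also says that the two arms are compared for all primary analyses.
- **Primary outcome.** Two measures stand under this heading. Cord compression degree is read before surgery on both static and dynamic MRI in every patient. For mJOA the text says: "The improvement rate of mJOA score at 3, 6, and 12 months compared to baseline will be calculated finally". No visit is singled out there.
- **Study design and Discussion.** The feasibility part compares the two MRI types. The validation part compares the randomised surgical plans.

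**The concern.** A trial should be tested at the error rate for which it was sized, and the two sections give different rates. The figure 0.025 can be read in three ways, and each leaves a sentence to correct:

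- As one two-sided test at 0.025, the analysis section doubles the alpha.
- As 0.05 split over two primary outcomes, testing each at 0.05 undoes the split.
- As one tail of a two-sided 0.05, the two sections agree in substance and two-sided is the wrong label for 0.025.

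The second issue is the primary time point. The sizing rests on 12 months, while the outcome section gives three visits equal standing. If that stays open until results are known, a favourable 3- or 6-month result could be put forward as the primary finding.

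**Working it through.** **1. Can N = 180 show which alpha was used?**

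Evaluable patients: 180 × 0.8 = 144, so 72 per arm. Difference: 85 − 60.8 = 24.2 percentage points.

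For two means, n per arm = 2 × SD² × (z_alpha + z_power)² / difference². The SD is not stated, so I solved for it: SD = 24.2 / [(z_alpha + z_power) × √(2/72)], where √(2/72) = 1/6.

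| Reading of 0.025 | z_alpha + z_power | Implied SD | Standardised difference |
|---|---|---|---|
| Two-sided 0.025 | 2.241 + 1.282 = 3.523 | 24.2 × 6 / 3.523 = 41.2 | 0.587 |
| 0.025 per tail (two-sided 0.05) | 1.960 + 1.282 = 3.242 | 24.2 × 6 / 3.242 = 44.8 | 0.540 |

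The two implied SDs are close, and the article gives nothing to choose between them. Treating 60.8% and 85% as proportions does not help either. The pooled two-proportion formula without continuity correction gives 82 per arm at two-sided 0.025, and 82/0.8 rounds up to 103, or 206 in total. At two-sided 0.05 it gives 69 per arm, and 69/0.8 rounds up to 87, or 174 in total. Neither is 180, and the article says a t-test was used. The stated N therefore cannot be reproduced without the SD and does not settle the alpha.

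**2. Error rate if only 12-month mJOA is confirmatory**

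At P < 0.05 it is 5%: twice the 0.025 stated for sizing, and equal to the stated analysis threshold.

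**3. Error rate if any of the three mJOA visits could count**

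I simulated three equally correlated standard normal statistics under no effect (2,000,000 draws per row), with critical value 1.960. The article gives no correlations, so these are assumptions.

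| Correlation | At least one false positive, either direction | Favouring dynamic MRI only |
|---|---|---|
| 0.5 | 12.5% | 6.3% |
| 0.7 | 10.9% | 5.5% |
| 0.8 | 9.9% | 4.9% |
| 0.95 | 7.4% | 3.7% |

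For a single visit the corresponding figures are 5% and 2.5%. Three independent tests would give 1 − 0.95³ = 14.3% in either direction. That is an upper figure, because repeated scores in the same patients are correlated.

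**4. Power under each way of reconciling the sections**

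Power ≈ Φ(standardised difference × √(72/2) − z_alpha), and √(72/2) = 6.

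- Sized at two-sided 0.025, tested at 0.025: Φ(3.523 − 2.241) = 90%.
- Sized at two-sided 0.025, tested at 0.05: Φ(3.523 − 1.960) = 94%.
- Sized at 0.025 per tail, tested at two-sided 0.05: Φ(3.242 − 1.960) = 90%.
- Sized at 0.025 per tail, tested at two-sided 0.025: Φ(3.242 − 2.241) = 84% (83% with the exact t distribution).

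**The case against.** The strongest case on the other side accepts that the two alphas differ and disputes most of what might be built on that.

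- **No rule says that any one significant result is success.** The P < 0.05 sentence is a general reporting convention that also covers secondary outcomes and correlations. The mJOA sentence says the rates will be calculated at three visits, not that each is a confirmatory test, and the sizing points to 12 months. This stands. A reader might infer that the false-positive rate is well above both 0.025 and 0.05. The article supports that only under an any-one-counts rule it does not state.
- **Cord compression should not be pooled with mJOA.** It is read before surgery, on both scans in every patient, and answers the feasibility question. It gives no second chance to claim a surgical benefit. This stands too. A reader might count four primary tests and reach about 14% to 17% (visit correlation 0.8 to 0.5, plus one independent test), but that mixes two questions. The statement that the arms are compared for all primary analyses invites the mistake and needs rewording.
- **Only false positives favouring dynamic MRI would support a superiority claim.** This is fair, and roughly halves the figures.
- **The 0.025 may be a mislabelled single tail.** This is possible and would leave only a wording error. It also means one cannot assume that testing at two-sided 0.025 is free of cost.
- **Multiplicity rules are commonly left to an analysis plan, which is not shown.** The absence of such a rule is accordingly not the point here. The point is two stated alphas that differ, and a primary outcome listed at three visits against a sizing at one. An unseen plan cannot make both sections right as written.

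**Conclusion.** The point holds in limited form. The sample size and statistical analysis sections conflict on alpha or on sidedness, and one of them must change. With 12-month mJOA as the sole confirmatory test, the applied error rate is 5%, double the sizing alpha if that was truly two-sided, and no more than 5%.

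The primary outcome section also leaves the confirmatory visit open. If any of the three visits could count, the rate is about 7% to 13% in either direction, or about 4% to 6% favouring dynamic MRI. Those ranges rest on assumed correlations of 0.95 to 0.5 and on a success rule that the article does not state, so they show what the wording permits and are not the trial's established error rate. Which alpha was used for 180 cannot be recovered without the SD; only the sponsor can say.

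**What to change.** 1. Confirm from the original calculation which alpha and sidedness gave 180. State the same pair in the sample size and statistical analysis sections, and give the SD.
2. In the primary outcome section, name the 12-month mJOA improvement rate as the single primary test of the randomised comparison, with 3 and 6 months secondary.
3. State that cord compression degree is the within-patient primary outcome of the feasibility part, and limit the sentence on comparing arms in all primary analyses to the randomised comparison.

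The cost is a few sentences and no additional patients. Power stays at 90% if 0.025 was truly two-sided and the analysis threshold is brought to 0.025. It also stays at 90% if the sizing was 0.025 per tail and the sample size section is corrected to two-sided 0.05. If the sizing was per tail and the test is instead tightened to two-sided 0.025, power falls to about 84% and the stated power must be revised. The change should be made before anyone sees outcome data by arm, since a later choice of visit or threshold could look driven by the results.
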